### 3.4.2 Analysis of mortality

The follow-up period for mortality is from date of baseline to date of death, or the date of follow-up assessment, whichever came first. For missing information on date of death, we will use the following strategies: (1) For participants who died during the baseline and 12-month follow-up, we impute the date using the median survival time of deceased participants at 12-months; (2) For participants who died during the 12-month follow-up and post-trial follow-up, we will impute the date using the median survival time of deceased participants who died during the post-trial period.

The cause of deaths will be classified by adopting the classification for cardiovascular mortality and stroke-related mortality used by the Global Burden of Diseases, Injuries, and Risk Factors Study. For missing information on cause of death, deaths will be classified as other causes of deaths.

Mortality rate for each mortality outcome will be estimated as the number of events divided by the total person-months since baseline. We will assess cumulative incidence of all mortality outcomes with the Kaplan-Meier curves, while accounting for village as clustering. Cox proportional hazards models using the generalized estimating equation (GEE) approach with an independence working correlation and robust sandwich variance will be used to compute hazard ratios (HRs) and 95% confidence interval (95% CIs) for the analysis with events and date of death as dependent variable. Age, sex, and township will be adjusted when estimating HRs. We will test adherence to proportional hazards assumption by plotting smoothed Schoenfeld residuals.

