### 3.2.2 Data collection for deceased participants

For deceased participants, we will employ a multifaceted approach to collect information on the date and cause of death from three major sources to gain the most reliable information. Firstly, we will utilize participants' unique ID numbers to link them to the local Center for Disease Control and integrate this data with the local death registration system. Secondly, to account for potential delays in the death records' updates, we will also independently collect vital status information through a standardized Excel form, including death dates and causes, from village doctors for all 50 villages. This information will supplement the CDC data. Thirdly, when there is key information missing or major inconsistency between two available sources, we will conduct a smartphone-based shortened version of verbal autopsy (VA) survey to informative family members of some selected dead participants by using Population Health Metrics Consortium (PHMRC) Shortened Questionnaire adult module. Trained health workers will conduct the VA interview. The procedure for the verbal autopsy survey will remain consistent with the one-year follow-up, with trained data collector administering a shortened version of the survey via smartphone to family members of deceased participants.

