#### *Mortality*

Mortality, an exploratory outcome of the original trial, will be considered as a key primary outcome of interests for the follow-up assessment considering the relatively long follow-up period. Date and cause of deaths will be collected from multiple approaches as mentioned above.

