| Physical measurement                                    |          |                  |                      |
| Time up and go                                                 | √        | √                | √                    |
| Height                                                         | √        | √                | √                    |
| Weight                                                         | √        | √                | √                    |
| Waist circumference                                            | √        | √                | √                    |
| Neck circumference                                             |          |                  | √                    |
| Grip strength                                                  |          |                  | √                    |
| Blood pressure                                                 | √        | √                | √                    |

2241

2242 **3.4 Statistical analysis**

2243 **3.4.1 General analysis**

2244 The analysis for major outcomes will be in the same way in line with the 12-month follow-up  
 2245 assessment, according to the published statistical analysis plan. The intention-to-treat principle  
 2246 will be used for all analyses. Descriptive analysis will be performed with means and standard  
 2247 deviations (SDs) or medians and quartiles for continuous variables, and counts and  
 2248 percentages for binary variables. The analysis of all continuous or binary outcomes, apart from  
 2249 mortality, remains consistent with the one-year follow-up statistical analysis plan. Specifically,  
 2250 for continuous variables, we will use mixed-effects linear regression to estimate differences  
 2251 between two arms in the outcomes from baseline to 12 months and 5.5-year post-baseline, with  
 2252 random intercept for village (cluster) and fixed effect for township. The main model will adjust for  
 2253 age, sex, and baseline outcome, and removed outliers based on an a priori decision to exclude  
 2254 values more than two interquartile ranges above the third quartile or below the first quartile of  
 2255 the distribution. In instances where the mixed effects model did not converge, we will employ  
 2256 the generalized estimating equations method by fitting a Gaussian model with an identity link.

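### Part B codes every death of unresolved cause as other causes and plans no check of what this does to cardiovascular and stroke mortality

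*Combined protocol and SAP*

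**What the plan says.** Part B, section 3.3.1 raises mortality from an exploratory outcome to a key primary outcome of the long-term follow-up and adds that "Date and cause of deaths will be collected from multiple approaches". Section 3.2.2 describes three sources. The first is linkage by ID number to the local CDC death registration. The second is a standard form from village doctors in all 50 villages, which supplements the registry. The third is verbal autopsy, used when an essential item is absent or the first two sources disagree materially. The autopsy interviews go to "family members of some selected dead participants".

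Section 3.4.2 then sets the categories: "The cause of deaths will be classified by adopting the classification for cardiovascular mortality and stroke-related mortality used by the Global Burden of Diseases". For whatever remains unresolved, the rule is: "For missing information on cause of death, deaths will be classified as other causes of deaths". The analyses that follow treat the coded cause as known. "Mortality rate for each mortality outcome will be estimated as the number of events divided by the total person-months since baseline", cumulative incidence is shown for all mortality outcomes, and HRs come from "Cox proportional hazards models using the generalized estimating equation (GEE) approach with an independence working correlation and robust sandwich variance".

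The sensitivity analyses in section 3.4.4 are extra covariate adjustment and the inclusion of outliers. None concerns missing cause. Section 3.4.1 sets mortality apart from the outcomes that follow the one-year SAP, and the pattern-mixture option in Part A, section 7.5 addresses loss to follow-up.

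**The concern.** The rule is a single-value imputation: no death of unresolved cause is ever cardiovascular or stroke-related. The plan's own background makes zero an unlikely value. Part A, section 1 attributes about 18.5% of all deaths in China to stroke alone, and every participant here has a history of stroke (Part A, section 5.2.3).

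Only the cause-specific analyses are at stake. Two things can happen to them. Event counts and rates for cardiovascular and stroke mortality fall by the number of such deaths left unresolved. And if the unresolved share differs between arms, the cause-specific HR moves, in either direction. Without counts of unknown cause by arm, a reader of the results could not tell whether either had happened.

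**Working it through.** **Plan's own figure.** There is none to reproduce on this point. The documents give no expected number of deaths, no mortality HR, no power for mortality and no missing-cause fraction. The only power figure (83%, Part A, section 5.3) concerns systolic blood pressure and has no bearing here.

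**Inputs from the documents.** The coding rule, the cause categories, the rate definition and the Cox model are in Part B, section 3.4.2. Follow-up for mortality "is from date of baseline to date of death, or the date of follow-up assessment, whichever came first", with the assessment about 5.5 years after baseline (section 3.4.1). Every fraction, rate and death count below is an assumption.

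**Step 1: effect on the rate.** Let u be the share of true cardiovascular (or stroke) deaths in an arm whose cause stays unresolved. Coding them as other gives

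observed rate = true rate × (1 − u).

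With u = 10% and an assumed true rate of 3.0 per 100 person-years, the observed rate is 3.0 × 0.90 = 2.7.

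**Step 2: effect on the HR.** Take other deaths as censored in the cause-specific model and u as constant over time within each arm. Then

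observed HR = true HR × (1 − u1)/(1 − u0), with 1 = intervention and 0 = control.

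| u1 | u0 | Multiplier | Observed HR if true HR is 1.00 | Observed HR if true HR is 0.80 |
|---|---|---|---|---|
| 10% | 10% | 0.90/0.90 = 1.00 | 1.00 | 0.80 |
| 5% | 10% | 0.95/0.90 = 1.06 | 1.06 | 0.84 |
| 10% | 5% | 0.90/0.95 = 0.95 | 0.95 | 0.76 |
| 5% | 15% | 0.95/0.85 = 1.12 | 1.12 | 0.89 |
| 15% | 5% | 0.85/0.95 = 0.89 | 0.89 | 0.72 |

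Fuller resolution of causes in the intervention arm moves the HR against the intervention; the reverse moves it in favour.

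**Step 3: check by simulation.** Two competing causes were simulated with constant hazards (assumed 0.03 cardiovascular and 0.02 other per year, 5.5 years, 150,000 per arm), and event-rate ratios were compared. At a true ratio of 1.00, the observed ratio was 1.12 for 5% versus 15% and 0.89 for 15% versus 5%. At 0.80 it was 0.88 and 0.71. At 0.80 with 10% in both arms it stayed at 0.80. This agrees with the formula within simulation error.

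**Step 4: equal shares cost events only.** Schoenfeld power is Φ(√(E/4) × |ln HR| − 1.96). With an assumed E = 150 cardiovascular deaths and HR 0.7, ignoring clustering, power is 58.9%. At u = 10% (E = 135) it is 54.5%, and at u = 20% (E = 120) it is 49.7%.

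**Step 5: what the added analysis would show.** Assume 100 deaths per arm, 60% truly cardiovascular in each, with 5 (intervention) and 15 (control) of unknown cause and the same 60% mix among the unknowns.

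| Unknown deaths counted as | Intervention | Control | Ratio |
|---|---|---|---|
| Other (plan's rule) | 57 | 51 | 1.12 |
| Cardiovascular in 60% | 60 | 60 | 1.00 |
| All cardiovascular | 62 | 66 | 0.94 |

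The two extremes enclose the true ratio here and show how far the answer depends on the rule. They apply the same assignment to both arms, so they are not the widest possible range. Opposite assignments by arm would give 62/51 = 1.22 and 57/66 = 0.86.

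**The case against.** The strongest reply is that little may be left for the rule to act on. Verbal autopsy is aimed at the deaths with missing or conflicting information, so the selection in section 3.2.2 targets the problem cases. The coding rule applies only to what survives registry, village doctor and autopsy. This stands, and it means the residual could be small. It does not remove the point: the wording leaves open whether every such death is reached, and section 3.4.2 needs a rule only because some causes may stay unknown.

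A reader might infer that missingness will differ by arm because village doctors supply causes and were not blinded (Part A, section 5.4, notes to the timeline diagram). The documents do not support that as a prediction. Village doctors only supplement the registry, on a standard form used in all 50 villages. Nothing makes the registry arm-dependent, and project support ended in July 2018, so most of the mortality follow-up comes later. Knowing the arm might affect which cause is reported; the documents do not show that it affects whether one is reported. The training and monthly visits in intervention villages make a difference possible, no more.

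A reader might also infer that rates are certainly too low in both arms. That holds only if some unresolved deaths in each arm were truly cardiovascular or stroke-related.

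Finally, sampling error may dominate. With 150 assumed cardiovascular deaths, and ignoring clustering, the standard error of the log HR is about 2/√150 = 0.163. The 95% interval then spans a factor of about exp(1.96 × 0.163) = 1.38 each way. A shift of 1.06 to 1.12 is small beside that, though the interval does not reflect it.

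**Conclusion.** The point holds for cardiovascular and stroke mortality only. The plan fixes at zero the probability that an unresolved death belongs to either category and provides no analysis that varies this. The rates are understated by the factor (1 − u) to the extent that unresolved deaths were truly of those causes. The HR changes only if u differs by arm: by 1.06 for 5% versus 10%, 1.12 for 5% versus 15%, 0.89 for 15% versus 5%, and not at all for equal shares. These shares are assumptions, since the documents allow no estimate of u in either arm, and the real effect may be negligible.

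Because section 3.3.1 lists mortality as a primary outcome, a reader might take the primary result to be at risk. All-cause mortality counts every death whatever its cause, so the rule does not touch it. This is a low-cost improvement to the cause-specific analyses; the documents do not show that those results will be biased.

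**What to change.** In Part B, section 3.4.2, keep unknown cause as a separate category after all three sources have been used, and report its count by arm. In section 3.4.4, add cause-specific HRs with all unknown deaths counted as cardiovascular (for the stroke outcome, as stroke), and then with all counted as other. The second is the plan's present rule. State this before causes are examined by arm.

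Multiple imputation of cause from baseline covariates and time of death is optional. It should not depend on place of death. The only place-of-death item shown is in the verbal autopsy form (Appendix A-5), so it may be absent for exactly the deaths that remain unresolved.

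The cost is a few sentences in the plan and one small extra analysis. No new data are needed.

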### 2139 **3.2 Procedures of follow-up assessment among participants**

2140 All surviving participants, regardless of their follow-up status at 12 months, of the SINEMA trial  
2141 will be invited to participate in a 5-year follow-up.

2142 Information on the vital status of the participants will be provided by village doctors, which  
2143 enabled the generation of a list of survival participants who are eligible to participate in the  
2144 survey and a list of deceased participants whose vital status, date and cause of deaths will be  
2145 further collected.

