### 3.2.3 Strategies to improve follow-up rate

To improve the follow-up rate, the following strategies will be performed: Participants whose village doctors informed that they have moved outside of the village, the last known residence will be contacted to provide the address and contact information of the participants if possible.

- (1) For participants who have relocated to other villages within the Nanhe county and in villages where the survey is planned, participants will be invited to participate in the survey of the corresponding villages.
- (2) For participants who have relocated within the county but in the area that were not involved in the SINEMA study, a team of researcher will contact them and schedule a door-to-door survey for follow-up assessment.
- (3) For participants who have relocated outside of the county, the research team and the data collection team will discuss the feasibility of performing data collection outside of the county.
- (4) Participants will be considered as lost to follow-up when known alive, but the participants were not able to complete the assessment following the previous mentioned procedure or refuse to participate in the study.

For patients with mental health issues or other severe diseases that may present difficulties for them to complete the survey, the data collection will be conducted with accompany of family member if possible. Family members may provide proxy responses to certain questions and the data collectors will label proxy responses where appropriate.

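### Part B's Kaplan-Meier curves overstate the cumulative incidence of cardiovascular and stroke death, and mortality follow-up has no stated end for survivors who are not assessed

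*Combined protocol and SAP*

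**What the plan says.** Part B section 3.3.1 raises mortality from an exploratory outcome of the trial to a key primary outcome of the long-term follow-up. Section 3.4.2 sorts deaths by "adopting the classification for cardiovascular mortality and stroke-related mortality" and then plans three summaries:

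- **Curves.** "We will assess cumulative incidence of all mortality outcomes with the Kaplan-Meier curves", with allowance for clustering by village.
- **Rates.** "Mortality rate for each mortality outcome will be estimated as the number of events divided by the total person-months since baseline".
- **Hazard ratios.** Cox models with a robust variance, adjusted for age, sex and township.

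Neither the protocol nor the analysis plan mentions a competing-risk estimator. Deaths without a recorded cause are handled by one rule: "For missing information on cause of death, deaths will be classified as other causes of deaths".

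The time at risk is set in the same section: "The follow-up period for mortality is from date of baseline to date of death, or the date of follow-up assessment, whichever came first". Part B section 3.2.3 describes people who may have neither date: "Participants will be considered as lost to follow-up when known alive, but the participants were not able to complete the assessment". Sections 3.2 and 3.2.2 take vital status from village doctors and deaths from registry linkage as well. Neither source requires the participant to attend.

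**The concern.** **Cause-specific curves.** A person who dies of cancer can no longer die of stroke. Kaplan-Meier for stroke death removes that person from the risk set as if the stroke death could still occur later. The result describes a hypothetical setting without other causes of death. It exceeds the proportion who actually die of stroke whenever competing deaths come before stroke deaths. Adjusting for clustering changes the confidence limits, not this. Readers would take the cardiovascular and stroke curves as absolute risks, and they would be too high in both arms.

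**End of follow-up.** Deaths are found whether or not a person attends, but the only end date written for a survivor is an assessment date. A survivor who is never assessed has no stated end date. The analyst must supply one, and if that is done after the data are seen, the choice can move the rates for a key primary outcome.

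**Working it through.** The documents give no mortality rate, event count, cause share or post-trial attendance figure, so there is no figure of the plan's own to reproduce. The inputs below are assumptions, except the horizon of 5.5 years from baseline, which is in Part B section 3.4.1.

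**Step 1: Kaplan-Meier against cumulative incidence.** Let F be all-cause risk at the horizon and s the share of deaths due to the cause, constant over time.

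- Cumulative incidence (Aalen-Johansen) = s × F
- 1 minus Kaplan-Meier = 1 − (1 − F)^s

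| F | s | s × F | 1 − (1 − F)^s | Excess, points | Excess, relative |
|---|---|---|---|---|---|
| 10% | 70% | 7.00% | 7.11% | 0.11 | 1.6% |
| 20% | 30% | 6.00% | 6.48% | 0.48 | 7.9% |
| 20% | 50% | 10.00% | 10.56% | 0.56 | 5.6% |
| 30% | 30% | 9.00% | 10.15% | 1.15 | 12.8% |
| 30% | 50% | 15.00% | 16.33% | 1.33 | 8.9% |

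Over F from 10% to 30% and s from 30% to 70%, the excess runs from 0.1 to 1.3 points and from 1.6% to 12.8% relative. With s = 100%, which is all-cause death, the two formulas agree. At F = 20% and s = 50%, the curves for the cause and for all other deaths add to 2 × 10.56% = 21.1%, against 20.0% who died.

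**Step 2: missing causes coded as other.** This rule works in the opposite direction. At F = 20% and s = 50%, 1 minus Kaplan-Meier falls back to 10.0% when the recorded share is ln(0.90)/ln(0.80) = 0.472. That is 1 − 0.472/0.50, or about 5.6% of the cause's deaths coded as other.

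**Step 3: known-alive non-attenders.** Take F = 20%, a constant hazard, and a share q = 10% of survivors not assessed.

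- Hazard = −ln(0.80)/5.5 = 0.04057 per year
- Person-years per participant with full follow-up = 0.20/0.04057 = 4.9296
- Non-attenders as a share of all participants = 0.10 × 0.80 = 0.08

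| Handling | Person-years per participant | Deaths per 1,000 person-years | Change |
|---|---|---|---|
| Followed to 5.5 years | 4.9296 | 40.57 | 0 |
| Censored at 12 months | 4.9296 − 0.08 × 4.5 = 4.5696 | 43.77 | +7.9% |
| Excluded | 4.9296 − 0.08 × 5.5 = 4.4896 | 44.55 | +9.8% |

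If non-attenders are excluded, all-cause risk becomes 0.20/(1 − 0.08) = 21.7%. Over F from 10% to 30% and q from 2% to 20%, early censoring or exclusion raises the rate by 1.4% to 23.4%.

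**Step 4: difference by arm.** Set control risk at 20% and the true rate ratio at 0.80. Intervention risk is then 1 − 0.80^0.8 = 16.35%, the hazard is 0.03246, and person-years are 5.037. Suppose 5% of intervention and 15% of control survivors are not assessed and are excluded:

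- Intervention: 0.1635/(5.037 − 0.05 × 0.8365 × 5.5) = 0.1635/4.807 = 34.01 per 1,000
- Control: 0.20/(4.9296 − 0.15 × 0.80 × 5.5) = 0.20/4.2696 = 46.84 per 1,000
- Ratio: 0.73, or 0.74 with censoring at 12 months

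Reversing the arms gives 0.89 and 0.87. With 10% in both arms the ratio stays at 0.80. These are ratios of person-time rates, used as a guide to what the Cox estimate would do.

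**The case against.** **On the curves.** The arms are compared by Cox hazard ratios and the curves are descriptive. Section 3.3.1 makes mortality a key primary outcome without singling out cardiovascular or stroke death. The excess is often about half a point and goes the same way in both arms. All of this stands, and it limits the importance of the point. The estimator is still the wrong one for the quantity named.

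A reader might infer that Part B's mortality figures are inflated in general. The documents do not support that. Kaplan-Meier is right for all-cause death, and neither the person-month rates nor the Cox models use it. Even the reported cause-specific figures have no certain net direction, because the missing-cause rule pulls them down (step 2). That is a separate classification matter and does not correct the estimator.

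**On the end of follow-up.** A reader might also infer that the plan drops known-alive non-attenders. No section says so. Section 3.4.1 applies intention-to-treat to all analyses, and vital status is collected outside the survey. Section 3.1 uses the term follow-up assessment for the whole 2018 survey wave, so the end date can be read as a common wave date, with little or no inflation. Section 3.2.3 plans tracing, home visits and proxy answers, which should keep the group small. Its definition of loss to follow-up concerns survey attendance and is not a censoring rule for mortality.

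These arguments turn this part into a missing definition. They do not supply it: sections 3.2.1 and 3.2.3 treat the assessment as something each participant completes, so both readings remain open.

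**Conclusion.** The first part holds as written in the plan. Kaplan-Meier curves for cardiovascular and stroke death overstate their cumulative incidence in both arms, by about 0.1 to 1.3 percentage points or 2-13% relative. The direction of the estimator error is certain; its size depends on the assumed mortality of 10-30% and cause share of 30-70%.

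The second part is a gap, with a conditional effect. At the assumed 20% mortality and 10% non-attendance, rates change by 0% if non-attenders are followed to the vital-status date, and by about +8% to +10% if they are censored at 12 months or excluded. A material shift in the hazard ratio needs early censoring or exclusion together with non-attendance that differs by arm, and nothing in the documents shows that either will happen.

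Both points should be settled before the mortality analysis. Neither undermines the all-cause comparison if non-attenders are followed to the vital-status date.

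**What to change.** In Part B section 3.4.2:

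1. Estimate cardiovascular and stroke-related mortality with the Aalen-Johansen cumulative incidence function, with deaths from all other causes as the competing event. Keep Kaplan-Meier for all-cause death.
2. Keep the Cox models and label the cardiovascular and stroke estimates as cause-specific hazard ratios. The estimates do not change.
3. Censor every participant not known to have died at the date vital status was last confirmed, by the village doctor or by registry linkage, whether or not the participant was assessed.
4. Report by arm the number known alive but not assessed.

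The cost is a few sentences and a few lines of code. Collection of vital status is already planned. The one practical addition is to keep the date on which each living participant's status was confirmed.
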